**Study protocol (English)**

Primary and Secondary Outcome Measures

1.1 Primary Outcome Measure

Change in hemoglobin (Hb) levels at 2 weeks after administration (2 weeks postpartum).

• Calculation: Value at 2 weeks after administration − Value at 0 weeks on the registration and administration start date.

Rationale:

To evaluate the improvement in anemia.

1.2 Secondary Outcome Measures

(1) Change in ferritin levels, Hb levels, and transferrin saturation (TSAT = serum iron ÷ TIBC × 100 (%)) at 4 weeks after administration (4 weeks postpartum).

(2) Changes in the Edinburgh Postnatal Depression Scale (EPDS) scores.

Rationale:

(1) To evaluate the improvement in anemia.

(2) To examine the impact of anemia on postpartum depression.

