1.3 Safety Outcome Measure

Incidence of adverse events.

Rationale:

Set as a general measure to evaluate safety.

2. Study Design

• Nature of the Study: Confirmatory

• Design: Parallel-group comparison

• Randomization: Randomized

• Blinding: Open-label (non-blinded)

• Control Group: Oral iron supplement treatment group

This study is a single-center randomized controlled trial targeting 60 postpartum women with iron deficiency anemia. To test the primary hypothesis, postpartum women with iron deficiency anemia (Hb <10 g/dL and ferritin <30 ng/mL) will be randomly assigned to receive either iron carboxymaltose injection or extended-release ferrous sulfate tablets.

Blinding is not possible due to the differences in treatment schedules between the iron carboxymaltose injection and extended-release ferrous sulfate tablets. Event evaluation will be conducted by a monitoring officer in a blinded manner using centralized assessment.

To verify the study hypothesis, the participation period for individual subjects is set at 1 month postpartum, referencing previous studies on postpartum iron deficiency anemia.

3. Patient Enrollment and Allocation

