4.1 Iron Carboxymaltose Injection

• Generic Name: Iron carboxymaltose injection

• Brand Name: Feinject Injection 500mg

• Approval Number: 23100AMX00290000

• Indications: Iron deficiency anemia

• Dosage: 500 mg administered intravenously once a week, maximum 1,500 mg total.

• Storage: Store at room temperature (avoid freezing).

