4.2 Extended-release Ferrous Sulfate Tablets

• Generic Name: Extended-release ferrous sulfate tablets

• Brand Name: Ferro-Gradumet 105mg tablets

• Approval Number: 22100AMX01333000

• Indications: Iron deficiency anemia

• Dosage: 105–210 mg of iron daily, taken 1–2 times a day on an empty stomach.

• Storage: Store at room temperature.

5. Observation and Examination Items

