5.6 Laboratory Tests

Blood tests will be conducted twice, requiring 10 ml of blood each time.

6. Target Number of Subjects and Planned Period

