4.2 Summary of Withdrawals or Discontinuations

A list of subjects who withdrew or discontinued will be provided.

5. Analysis Plan for Subject Background

Summary statistics of baseline characteristics will be calculated for each analysis population by group.

For categorical variables, the frequency and percentage will be shown. For continuous variables, summary statistics (sample size, mean, standard deviation, minimum, 1st quartile, median, 3rd quartile, and maximum) will be presented.

Between-group comparisons will be made using Pearson’s chi-square test for categorical variables (Fisher’s exact test if more than 20% of expected frequencies are below 5) and Student’s t-test or the Wilcoxon rank-sum test for continuous variables. A two-sided significance level of 5% will be used.

6. Analysis Plan for Primary Outcome

The primary objective of this study is to demonstrate the superiority of iron carboxymaltose injection over extended-release ferrous sulfate tablets in terms of the change in Hb levels at 2 weeks postpartum.

The primary outcome will be analyzed by comparing the mean change in Hb levels between the two groups. The null hypothesis is that the mean change in Hb for the treatment group is equal to that of the control group (mean change difference = 0), and the alternative hypothesis is that the mean change differs between the groups.

A two-sided 95% confidence interval for the mean change difference will be calculated. Covariate-adjusted ANCOVA will be used, adjusting for factors such as delivery mode (vaginal delivery or cesarean section), severity of anemia (Hb < 8 g/dL or Hb ≥ 8 g/dL), and baseline Hb levels.

7. Analysis Plan for Secondary Outcomes

To supplement the primary analysis, secondary outcomes will be analyzed without adjusting for multiplicity. A two-sided significance level of 5% and 95% confidence intervals will be calculated.

The change in ferritin, Hb, and TSAT levels at 4 weeks postpartum will be summarized by sample size, mean, standard deviation, minimum, 1st quartile, median, 3rd quartile, and maximum. Covariate-adjusted ANCOVA will be used to analyze these outcomes.

EPDS score progression will be evaluated by calculating the proportion of subjects with scores ≥ 9 at baseline and at 4 weeks postpartum. Between-group comparisons will be conducted using the chi-square test and adjusted Mantel-Haenszel test (risk difference) with covariates for delivery mode and severity of anemia.

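### The week-4 serum iron sample is not timed against study-drug intake, so a recent tablet may raise TSAT mainly in the oral arm

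*Combined protocol and SAP*

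**What the plan says.** - **Outcome.** Protocol section 1.2 and statistical protocol section 1.3 define the measure identically: "transferrin saturation (TSAT = serum iron ÷ TIBC × 100 (%)) at 4 weeks after administration". Neither gives a time of day or an interval since the last dose.
- **Sampling.** The whole of protocol section 5.6 reads: "Blood tests will be conducted twice, requiring 10 ml of blood each time". Sections 5.1 to 5.5 list no time of draw and no time of last tablet or infusion.
- **Oral arm.** Section 4.2: "105–210 mg of iron daily, taken 1–2 times a day on an empty stomach". No duration is given.
- **IV arm.** Section 4.1: "500 mg administered intravenously once a week, maximum 1,500 mg total". No window or latest date is given.
- **Follow-up.** Section 2: "the participation period for individual subjects is set at 1 month postpartum".
- **Analysis.** Statistical protocol section 7: "Covariate-adjusted ANCOVA will be used to analyze these outcomes". The covariates for the secondary outcomes are not listed. Those named for the primary outcome in section 6 are delivery mode, anemia severity and baseline Hb; none concerns dose timing.

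Two sections, 3.2 of the protocol and 9.1 of the statistical protocol, were not in the text available. By their numbering they belong to enrollment and allocation and to analysis implementation, so neither is a likely place for a sampling rule.

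**The concern.** Serum iron is the numerator of TSAT, so any short-lived rise in it passes straight into the outcome. The two arms are dosed on different rhythms. A woman on daily tablets may have taken one within hours of the week-4 draw. A woman given weekly infusions on time had her last about two weeks earlier. If an oral dose raises serum iron for a while, the week-4 comparison mixes iron status with time since the last tablet, and it does so mainly in one arm.

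Randomization balances what the women bring to the trial, not a measurement effect that one arm's schedule creates afterwards. Adjusting for delivery mode, anemia severity and a baseline value does not remove it either. If intake times are not collected, nobody can tell later whether the TSAT result was affected. At stake is the reading of one secondary laboratory measure.

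**Working it through.** **The plan's own figures.** The documents give no serum iron, TIBC or TSAT value and no post-dose rise, so there is no TSAT figure to reproduce. The only design figure is 60 women, 30 per arm, stated without effect size, SD, power or dropout, so it cannot be reproduced either. For scale, at two-sided 5% and by the normal approximation, 30 per arm detects a standardized difference of (1.960 + 0.842) × √(2/30) = 0.72 at 80% power, or (1.960 + 1.282) × √(2/30) = 0.84 at 90%.

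**Step 1: interval from last dose to the week-4 draw.** 1,500 mg ÷ 500 mg = 3 infusions at most. Given weekly without delay, they fall 0, 7 and 14 days after the start, so the last is 28 − 14 = 14 days before week 4. Daily tablets, if still being taken, leave at most about 1 day.

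**Step 2: from serum iron to TSAT.** At fixed TIBC, the rise in TSAT is h = 100 × (rise in serum iron) ÷ TIBC. All inputs here are assumptions.

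| Assumed rise in serum iron (µg/dL) | h at TIBC 450 µg/dL | h at TIBC 300 µg/dL |
|---|---|---|
| 10 | 2.2 | 3.3 |
| 20 | 4.4 | 6.7 |
| 40 | 8.9 | 13.3 |
| 80 | 17.8 | 26.7 |

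The next step uses h = 3, 6 and 12 points. At a TIBC of 400 µg/dL, the ends of that range need a serum iron rise of 3 × 400/100 = 12 and 12 × 400/100 = 48 µg/dL.

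**Step 3: shift in the arm difference.** If a share f of oral women is sampled while serum iron is raised, the IV − oral difference moves by −f × h.

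| f | h = 3 | h = 6 | h = 12 |
|---|---|---|---|
| 25% | −0.75 | −1.5 | −3 |
| 50% | −1.5 | −3 | −6 |
| 100% | −3 | −6 | −12 |

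**Step 4: effect on the test.** Assume an SD of change of 10 points and a true IV advantage of 10 points. Without any shift, power is Φ(10 ÷ (10 × √(2/30)) − 1.96) = Φ(1.91) = 97%. With a shift, the difference is 10 − f × h, the oral-arm variance becomes 100 + f(1 − f)h², and the pooled SD is the root of the mean of the two arm variances. For f = 50% and h = 6: difference 7, oral variance 109, pooled SD √104.5 = 10.2, power Φ(7 ÷ 2.64 − 1.96) = 76%. Power to show an IV advantage is then:

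| f | h = 3 | h = 6 | h = 12 |
|---|---|---|---|
| 25% | 95% | 90% | 72% |
| 50% | 91% | 76% | 30% |
| 100% | 77% | 34% | under 1% |

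In the last cell the expected difference is 10 − 12 = −2, a reversal. With no true difference and an SD of 10 in both arms, a shift of 0.75, 3 or 6 points raises two-sided rejection from 5% to about 6%, 21% or 64%, almost all in favor of oral iron.

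**The case against.** A reader might infer that tablet iron does inflate TSAT in the oral arm alone and does bias the comparison. The documents do not support that as fact:

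- They contain no post-dose serum iron data for this extended-release product. That a tablet raises serum iron appreciably is itself an assumption, and the size may be negligible.
- Section 4.2 gives no tablet duration. One month of participation is not a one-month course. If tablets stop well before week 4, the point falls away.
- Section 4.1 sets no window for the infusions. A delayed third infusion shortens the 14-day gap, so the most that can be said is mainly the oral arm.
- No case report form or laboratory manual is available. Intake times are not mentioned in section 5; that does not show they go unrecorded.

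A reader might also infer from the baseline wording, which refers only to the day treatment starts, that the week-0 sample could follow the first dose. That reading is weak. Entry requires Hb and ferritin results (section 2), eligibility is confirmed before treatment (section 3.1), and allocation is stratified on Hb (section 3.3). Serum iron is not an entry criterion, but statistical protocol section 2.3 sets the baseline against a measurement after the intervention. Together these imply a pre-treatment baseline.

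Finally, TSAT is one of three laboratory measures within one secondary outcome, and the possible error runs against IV iron, so it could not create a false IV advantage.

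All of this limits the claim. What survives is that the text sets no sampling condition for an outcome that could depend on one, while the arms' schedules differ in exactly the relevant respect.

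**Conclusion.** The point holds conditionally and is minor. It needs tablets to be still in use at week 4, infusions given without material delay, and a recent tablet that raises serum iron. Under those conditions, week-4 TSAT may be raised mainly in the oral arm, which would shrink or reverse an apparent IV advantage on that measure. On the assumed ranges the shift is 0.75 to 12 points against IV, and the documents do not fix where in that range, or below it, the truth lies. Ferritin and Hb are not calculated from serum iron, so the primary outcome and the other week-4 laboratory outcomes stand. It is worth acting on because the remedy is cheap and, without intake times, a surprising TSAT result could not be explained afterwards.

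**What to change.** - **Section 5.6.** State that the week-4 serum iron and TIBC sample, in both arms, is drawn before any study-drug intake that day. Record the clock time of the draw and of the last tablet or infusion. Dosing stays as it is. A tablet taken the previous evening can still precede the draw by less than a day, so the recorded times are needed as well as the rule.
- **Statistical protocol section 7.** Describe time since last dose by arm, and interpret TSAT alongside ferritin. Do not add an analysis restricted to pre-intake samples. That would select on a post-randomization variable which a woman on daily tablets can fail and a woman with no infusion that day cannot, so it would set a self-selected oral subset against nearly the whole IV arm.
- **While editing 5.6.** Reconcile its two blood tests with sections 1.1 and 1.2, which need values at weeks 0, 2 and 4. Whether all three draws are planned comes before the timing of any one of them.
- **If samples have already been taken.** Retrieve whatever draw and intake times exist, disclose the limitation, and read TSAT with ferritin.

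The cost is one sentence, two case report form fields, a descriptive table and a slight constraint on appointment times.

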1.3 Safety Outcome Measure

Incidence of adverse events.

Rationale:

Set as a general measure to evaluate safety.

2. Study Design

• Nature of the Study: Confirmatory

• Design: Parallel-group comparison

• Randomization: Randomized

• Blinding: Open-label (non-blinded)

• Control Group: Oral iron supplement treatment group

This study is a single-center randomized controlled trial targeting 60 postpartum women with iron deficiency anemia. To test the primary hypothesis, postpartum women with iron deficiency anemia (Hb <10 g/dL and ferritin <30 ng/mL) will be randomly assigned to receive either iron carboxymaltose injection or extended-release ferrous sulfate tablets.

Blinding is not possible due to the differences in treatment schedules between the iron carboxymaltose injection and extended-release ferrous sulfate tablets. Event evaluation will be conducted by a monitoring officer in a blinded manner using centralized assessment.

To verify the study hypothesis, the participation period for individual subjects is set at 1 month postpartum, referencing previous studies on postpartum iron deficiency anemia.

3. Patient Enrollment and Allocation

3.1 Patient Enrollment Method

The following procedure will be followed to promptly enroll patients after obtaining written consent:

(1) The principal investigator or researchers will obtain written consent from the subject and confirm eligibility.

(2) Eligible subjects will be assigned identification codes prior to study treatment initiation.

(3) Study treatment will be initiated according to allocation results.

3.3 Allocation

• Allocation Ratio: 1:1

• Method: Stratified block randomization

• Adjustment Factors: Mode of delivery (vaginal delivery, cesarean section), severity of anemia (Hb < 8 g/dL, Hb ≥ 8 g/dL).

• Rationale for Adjustment Factors: To account for differences in blood loss during delivery and the effect of anemia treatment based on anemia severity.

3.4 Person in Charge of Patient Enrollment and Allocation: [name]

The person responsible for drug allocation will create an allocation table consisting of serial numbers, randomized orders of the control drug and active drug names (iron carboxymaltose injection or Ferro-Gradumet tablets), and study drug allocation codes.

4. Drugs (or Medical Devices) Used in the Study

4.1 Iron Carboxymaltose Injection

• Generic Name: Iron carboxymaltose injection

• Brand Name: Feinject Injection 500mg

• Approval Number: 23100AMX00290000

• Indications: Iron deficiency anemia

• Dosage: 500 mg administered intravenously once a week, maximum 1,500 mg total.

• Storage: Store at room temperature (avoid freezing).

4.2 Extended-release Ferrous Sulfate Tablets

• Generic Name: Extended-release ferrous sulfate tablets

• Brand Name: Ferro-Gradumet 105mg tablets

• Approval Number: 22100AMX01333000

• Indications: Iron deficiency anemia

• Dosage: 105–210 mg of iron daily, taken 1–2 times a day on an empty stomach.

• Storage: Store at room temperature.

5. Observation and Examination Items

5.1 Patient Background

Age, body weight at delivery, height, mode of delivery, blood loss during delivery, gestational age at delivery.

5.2 Subjective Symptoms and Objective Findings

Confirmed through questionnaires and visual inspection at each visit.

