5.3 Observation of Adverse Events

All adverse events will be recorded, including severity, seriousness, causal relationship, onset time, outcome, and resolution time.

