8.1 Safety Outcome Analysis Plan

The primary safety outcome is the frequency and proportion of adverse events. Adverse event data will be summarized by the number of cases and proportion in each group, with 95% exact binomial confidence intervals. Between-group comparisons will be made using Pearson’s chi-square test (Fisher’s exact test if needed).

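### Weekly infusions bring IV-arm women in at week 1, no week-1 contact is stated for the oral arm, and symptoms are asked about per visit, so adverse events may be solicited more often on IV iron

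*Combined protocol and SAP*

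**What the plan says.** - **How symptoms are found.** Protocol section 5.2: "Confirmed through questionnaires and visual inspection at each visit". No time points and no recall period are given.
- **What is recorded.** Protocol section 5.3: "All adverse events will be recorded, including severity, seriousness, causal relationship, onset time, outcome, and resolution time". This sets the content of the record, not when or how women are asked.
- **IV regimen.** Protocol section 4.1: "500 mg administered intravenously once a week, maximum 1,500 mg total".
- **Oral regimen.** Protocol section 4.2: "105–210 mg of iron daily, taken 1–2 times a day on an empty stomach". No dispensing visit or other contact is mentioned.
- **Assessment times common to both arms.** Sections 1.1 and 1.2 of the protocol, and 1.2 and 1.3 of the statistical protocol, use baseline, week 2 and week 4. Section 5.6 gives a number of blood tests but no visit calendar. Section 2 states that "the participation period for individual subjects is set at 1 month postpartum", without distinguishing the arms.
- **Blinding.** Section 2: "Blinding is not possible due to the differences in treatment schedules between the iron carboxymaltose injection and extended-release ferrous sulfate tablets". The same section adds: "Event evaluation will be conducted by a monitoring officer in a blinded manner using centralized assessment".
- **Analysis.** Section 8.1 of the statistical protocol compares the proportion of women with adverse events by Pearson's chi-square or Fisher's exact test. It defines no common ascertainment window and makes no allowance for number of contacts.

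**The concern.** A proportion with any adverse event depends on how often women are asked as well as on how often events occur. Here asking is linked to visits, and one regimen generates visits that the other does not obviously generate. A brief symptom in the first week could be noted at an infusion visit on IV iron, but go unrecorded on tablets if it has resolved and is not recalled by week 2.

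Safety relative to oral iron is part of the stated purpose (statistical protocol, section 1). If asking is unequal, an excess on IV iron could be partly an artefact, and a true excess on tablets could be hidden. Blinded central evaluation does not help with this: it can classify the events it receives, but cannot supply events that nobody asked about.

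**Working it through.** The documents give no visit count, adverse event rate or ascertainment figure, so there is no stated number to reproduce.

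**Step 1: contacts implied by the text.** Maximum infusions = 1,500 / 500 = 3. Given in consecutive weeks, they fall at weeks 0, 1 and 2. Weeks 0 and 2 are already assessment times for both arms, so the dosing schedule adds at most one contact, at week 1. Post-baseline occasions for asking are then weeks 1, 2 and 4 on IV iron, and weeks 2 and 4 on oral iron if the oral arm has no week-1 contact.

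**Step 2: illustration of size.** All of these are assumptions, not document figures:
- the true risk is the same in both arms;
- each post-baseline questionnaire picks up a new event with probability p;
- every IV-arm woman has a week-1 contact and no oral-arm woman does;
- oral-arm women report a share r of their week-1 events when asked at week 2.

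The formulas are:
- IV proportion = 1 − (1 − p)³
- Oral proportion = 1 − (1 − rp)(1 − p)²
- Spurious excess = p(1 − r)(1 − p)²

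For example, with p = 0.10 and r = 0, IV is 1 − 0.9³ = 0.271, oral is 1 − 0.9² = 0.190, and the excess is 0.081. With r = 0.5, oral is 1 − 0.95 × 0.81 = 0.2305 and the excess is 0.0405.

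| p | IV, % | Oral with no recall, % | Excess, r = 0 | Excess, r = 0.5 | Excess, r = 0.8 | Excess, r = 1 |
|---|---|---|---|---|---|---|
| 0.05 | 14.3 | 9.8 | 4.5 | 2.3 | 0.9 | 0 |
| 0.10 | 27.1 | 19.0 | 8.1 | 4.05 | 1.6 | 0 |
| 0.20 | 48.8 | 36.0 | 12.8 | 6.4 | 2.6 | 0 |
| 0.30 | 65.7 | 51.0 | 14.7 | 7.35 | 2.9 | 0 |

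Excess is in percentage points. With 30 women per arm (protocol section 6.1), 8.1 to 14.7 points is 30 × 0.081 = 2.4 to 30 × 0.147 = 4.4 women. If only a fraction f of IV-arm women have a second infusion, the excess is multiplied by f. The documents do not give f.

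**Step 3: effect on the planned test.** The rejection probability was enumerated exactly for two arms of 30 at two-sided 5%. Fisher's test was used when more than 20% of expected counts were below 5; that rule is stated in section 5 of the statistical protocol and is assumed to apply in 8.1. With no recall, the chance of a significant difference although true risks are equal is 3.6%, 10.8%, 17.0% and 21.0% for p = 0.05, 0.10, 0.20 and 0.30. Nearly all of this is in the direction of more events on IV iron (3.4%, 10.5%, 16.9% and 20.9%). With equal numbers of contacts the rate is about 1 to 5%.

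**The case against.** The strongest objection is that the central fact is not written down. No section gives a visit schedule for either arm. The remark in section 2 concerns treatment schedules, not assessment schedules, and silence about oral-arm attendance is not a statement that these women stay away. In addition, 1,500 mg is a maximum, so the number of infusions after baseline is not fixed. This stands. A reader might infer that the comparison is biased against IV iron by design. The documents do not support that, because both the existence and the size of any bias depend on a schedule they do not state.

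A second objection is that section 5.3 requires all adverse events to be recorded with onset and resolution times, so first-week events can be captured later. This stands in part. The rule is not limited to events found at visits, and good recall shrinks the excess towards zero. But it does not say that the week-2 questionnaire must cover the whole interval since baseline, and it does not equalise how often women are asked.

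A third is that the 8 to 15 point range is a worst case. That is correct: it assumes that the oral arm recalls nothing from week 1, and it should not be quoted without the half-recall and full-recall figures.

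**Conclusion.** The point holds as a conditional one. As written, only IV-arm women who receive a second infusion have a documented reason to be seen at week 1, and symptoms are solicited at each visit. Unless oral-arm women are also seen then, asking is more frequent on IV iron, and the section 8.1 comparison may be tilted against it. If there is an imbalance from this source, it runs in that direction.

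Its size cannot be derived from the documents. For an assumed pick-up of 10 to 30% per questionnaire, equal true risk and a second infusion for every IV-arm woman, it is about 8 to 15 points with no recall of week-1 events and about 4 to 7 points with half recall. It is zero with full recall, or if the oral arm attends at week 1. At 5% pick-up the excess is 4.5 points at most, and the false-significance rate stays below 5%. The primary hemoglobin comparison is not affected by this mechanism. The change is a cheap improvement, not the repair of a demonstrated bias.

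**What to change.** In protocol sections 5.2 and 5.3, specify the same symptom questionnaire at the same time points in both arms: weeks 1, 2 and 4, each form covering the period since the last one. Oral-arm women not seen in clinic at week 1 complete that form themselves. The same should apply to any IV-arm woman who does not attend that week. If the oral arm is already seen at week 1, a sentence saying so, with the recall period, is enough.

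In section 8.1 of the statistical protocol, state that all adverse events, including those observed at infusion visits, stay in the between-arm comparison. Restricting the test to events found at weeks 2 and 4 and listing infusion-visit events separately may look tidier. It could remove genuine infusion-related events from the test and understate harm on IV iron.

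The cost is some wording and one short extra form for the oral arm. Treatment and sample size do not change. One limitation remains: at week 1 a self-completed form may not yield the same reports as questioning and inspection in clinic, so the imbalance is reduced but may not be fully removed.
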